**RESEARCH PROJECT**

**3 – INTRODUCTION**

Dentin hypersensitivity (HD) is defined as: "Acute and short-lived pain from exposed dentin on a thermal, evaporative, tactile, osmotic or chemical stimulus, and which cannot be attributed to any other form of dental defect or pathology ". (1,2,3) The reported pain is of short duration and is remission when the stimulant is withdrawn, affecting the patients' quality of life, which can compromise daily activities such as brushing teeth, eating, drinking, and even social interaction. (4,5)

Non-carious cervical lesions (LCNC) are characterized by the irreversible loss of cervical tooth structure at the cement-enamel junction level (JCE). Among the etiological factors of these lesions we have stress, biocorrosion and friction, and according to the factor that predominates in their development the LCNC are divided into: Abfraction that results mainly from the occlusal trauma that produces tensions in the JCE, generating microfractures in the enamel and dentin exposure. Dental brushing, associated with biocorrosion due to changes in diet, produces tooth wear. (2,6) Because of the irreversible loss of cervical tooth structure that originates, any LCNC could be linked to the development of HD. (7)

Loss of gingival-tooth bonding or gingival recession is another factor related to the exposure of the dentinal tubules at the cemento-enamel junction. Since the rate of cement resorption is greater than that of dentin, a root exposure increases, increasing the probability of opening the dentinal tubules to the oral medium, this whole cycle results in HD. (8)

The hydrodynamic theory of Brännström is accepted to describe the origin of HD, which is initiated by thermal, mechanical or chemical stimuli acting on the exposed dentin tubules, altering the movement of the fluid inside them and stimulating the response of the fibers A-β and A-δ (which are surrounding the odontoblasts), which react in the form of pain. (1,2) According to this theory, the best treatment for sensitivity is the reduction of fluid movement within the tubules by obstructing them, or by limiting the nerve response. (9)

The ideal desensitizing material should exhibit rapid action, long-term effect, be biocompatible, non-irritating to the pulp, painless, easy to apply, and not cause tooth color change. (10,11) The fluorinated amorphous calcium casein-phosphate (CPP-ACPF) phosphopeptide may be useful in reducing HD because of its ability to incorporate into the surface of the enamel and dentin, acting as a reservoir of calcium and phosphate, occluding the dentinal tubules, avoiding the movement of liquid inside them, preventing the stimulation of the nerve fibers, and therefore the HD. (12)

Casein phosphopeptides (CPP) originate by enzymatic hydrolysis of casein. CPP has multiple phosphoserine residues, which interact and bind to calcium and amorphous phosphate (ACP) ions stabilizing them in an aqueous solution, forming the CPP-ACP complex. When fluoride is added, it becomes phosphopeptide of casein-fluorinated amorphous calcium phosphate (CPP-ACPF), which is more effective than CPP-ACP to inhibit enamel demineralization and facilitate remineralization of enamel early lesions by the availability of high concentrations of calcium and phosphate. (13,14)

Low power laser therapy (TLBP) involves the noninvasive application of red light (600-700 nm) and near infrared (700-950 nm), with a power density (irradiance) between 01 mW and 5 m W / cm2, (15) being increasingly employed in medicine and dentistry due to its analgesic, anti-inflammatory and biostimulating effects. It acts by inducing the production of mitochondrial adenosine triphosphate (ATP), increasing the presence of β-endorphin, and by inhibiting the enzyme cyclooxygenase, which transforms arachidonic acid into prostaglandins, attenuating the perception of painful stimuli in dentin tissues. (16) TLBP also reduces dentin sensitivity by means of photobiomodulation of the dental pulp, generating an increase in the cellular activity rate of odontoblasts, increasing its production of tertiary dentin, thus obliterating the dentinal tubules. (17,18)

**4 - JUSTIFICATIVE**

The prevalence of HD ranges from 8% to 74% according to the population evaluated and the technique used for its diagnosis. (8, 19, 20, 21) But almost all studies agree that the predominant location is in the canines and first premolars, followed by incisors and second premolars. (22) An investigation in the Northwest of the United States evaluated 787 adult patients and found a prevalence of 12.3% in the 18-44 age group, predominating in women, and associated with periodontal disease, gingival recession, or erosive exposure. (23) Of the 300 Brazilian patients, 46% had HD, with a mean age of 40 years, where toothbrushing four times a day and with excessive force, bruxism and / or gastroesophageal reflux were associated factors. (24)

Now, in countries such as Canada, with a history of long-term preventive dentistry, consequently there is a large number of elderly teeth, and according to the Canadian Advisory Board (1), this makes the prevalence rate of HD in this country from 25 to 30% of the population and can not be related to age. However, the same situation can not be extrapolated worldwide, it is estimated that a quarter of its population suffers from HD, although this is not a lethal disease, but it is clinically relevant since it severely compromises the quality of life of its patients . Therefore, the evaluation of effective and long-lasting desensitizing treatments is necessary to address the consequences of HD. (25)

Dentin and pulp have the same ectomesenchymal embryological origin and are closely related, that is, the physiological and / or pathological reactions in one tissue will affect the other. (26, 27) Dentin has a large amount of dentin tubules, and each one is occupied by an odontoblastic process and the surrounding dentin, the latter being responsible for communicating the pulp to the outermost regions of the dentin. When the dentine is exposed by loss of enamel or cementum suprajacent, changes in the medium may affect the histophysiology of its dentin fluid, and consequently the nerve fibers of the dentin-pulp complex generating pain, which may be reduced by occlusion of the tubules exposed. (27, 28)

Absi et al. (29) reported the correlation between HD and dentin tubule density. By means of scanning electron microscopy (SEM), they determined that, in sensitive teeth, the number of open tubules and their amplitude were respectively eight and two times higher when compared to teeth without HD. In physics, the flow of the liquid is proportional to the fourth power of the radius, indicating that twice the diameter in the teeth with HD generates a 16 times greater flow than in the healthy teeth. (2,22)

For the development of HD, two events are essential: "lesion location" - dentin is exposed by removal of enamel or dental cementum, and "initiation of injury" - by opening the dentinal tubules to the buccal environment. (1, 3, 22) Since treatments that occlude the dentinal tubules are ideal for reducing HD, however, their efficacy will depend on their resistance to the various challenges of the oral environment. (3)

CPP-ACP is a milk protein derived complex marketed as an additional source of calcium and phosphate ions. When fluoride is added to the CPP-ACP, the deposition of calcium, phosphate and fluoride ions on the tooth, the apatite crystals reorganize and the surface remineralize, recovering the properties of the dental structure. (30, 31)

Due to the low solubility of calcium phosphate ions (PCA) and their poor adhesion to the dental surface, a stabilizing agent is required, such as casein phosphate (CPP) whose multiple phosphorylated serine groups solubilize and stabilize the ACP , maintaining high concentration gradients of calcium and phosphate ions in a demineralised lesion, promoting high rates of enamel remineralization. (32, 33)

Similarly, fluorine is a remineralizing agent by being converted to fluorapatite (FA). However, to form one unit of FA, ten calcium ions and six phosphate ions are required for every two fluorine ions (Ca10 (PO4) 6 F2), and consequently the availability of calcium and phosphate ions restricts the formation of the remineralizing network by the fluorine. CPP-ACPF has a synergistic effect on dental remineralization, since CPP-ACP increases the concentration of calcium and bioavailable phosphate ions, thereby increasing the incorporation of fluoride ions into the dental biofilm, as well as, in the subsurface lesions of enamel in the form of FA. (13, 34, 35)

When CPP-ACP and a placebo gel were evaluated, under the effect of decreasing HD during 6 months, CPP-ACP demonstrated a rapid and stable reduction of HD during follow-up, whereas placebo generated an improvement moderate, but this was not statistically significant. (36) This is in agreement with Tung et. Al 1992, which demonstrated that, at high concentrations, CPP-ACP precipitates amorphous calcium phosphate, which, being the main inorganic component of the tooth, decreases dentin permeability by 85%, acting as an excellent tubular obliterator. (36)

On the other hand, TLBP has been applied to promote wound healing, reduce inflammation, and alleviate chronic and acute pain. This latter effect is related to the suppression of the activity of the substance P and bradykinin, serotonin release, improved circulation reduction in the production of acid metabolites that stimulate pain receptors, and deceleration of the action potential velocity, inhibiting the electrical conduction of Fibers C and Aδ, and modulating the pain threshold. However, the therapeutic effects of TLBP are subject to the application of certain wavelengths, laser intensity, location and optical properties of treated tissues. (15)

The diode laser of arsenic gallium and aluminum (AsGaAl), with a wavelength of 810 nm, increases the action potential of nerve cells, thus limiting the transmission of painful stimuli, but without heating the dental surface to the degree of generating modifications in the same. (37) With other wavelengths, the increase in energy in the dental surface leads to dentin fusion, and reduction of the diameter or obliteration of the dentinal tubules. (9, 38) A recent systematic review has shown that AsGaAl laser is more effective in reducing HDD in the long term than certain desensitizing agents without causing pulpal damage, allergy, or obvious clinical complications. (21)

However, although there are multiple treatments to reduce HD, none of them are considered a "gold standard", since the most commonly used desensitizing agents are effective in the short term, with an unstable response rate in more extended times (39,40) the need for clinical trials to evaluate the effectiveness of desensitizing treatments over time and to clarify the methodology and ideal product for the treatment of this disease due to the impact on the quality of life of its patients.

CPP-ACPF and TLBP present the ability to reduce dentin sensitivity by obliterating the dentinal tubules, and their association could generate a synergistic effect, being a more effective way of treating HD, justifying the purpose of this study.

**RESEARCH PROJECT**

**5 – AIM**

The aim of this study was to evaluate the effect of the fluorinated amorphous calcium phosphate casein-phosphorus (CPP-ACPF) associated with low-power laser therapy (TLBP) on the symptomatology and impact of the quality of life of patients with dentin hypersensitivity ( HD) by means of a randomized, parallel, placebo-controlled clinical trial. The null hypothesis tested in the present study will be:

H0 - there will be no difference in the manifestation of dentin hypersensitivity between the groups treated with TLBP, CPP-ACPF or placebo, associated or not, during one month of evaluation, and will not influence the participants' quality of life.

**6 – METHODOLOGY**

## **6.1. Ethical aspects**

This research project will follow the recommendations of the CONSORT (Consolidated Standards of Reporting Trials), (41). The research participants will be duly informed and informed about the risks, methods and objectives of this project. It is necessary to sign the informed consent form (TCLE) in accordance with the Helsinki declaration before starting treatment.

The information to be collected was exclusively scientific and the identity of the participants was preserved throughout the study. Participation in the study could be canceled and the consent term withdrawn at any time from the research, ensuring confidentiality of the participant even in case of abandonment of the treatment.

**6.2. Sample selection**

Students and employees of the Federal University of Pará, Belém, Pará, Brazil, between 18 and 50 years old, of both sexes, will be evaluated and recruited at the Faculty of Dentistry of the Federal University of Pará, Belém, Pará, Brazil. The inclusion and exclusion criteria are described in Table 01.

Two calibrated dentists evaluated potential candidates. Firstly, using a tactile stimulus: by sliding an exploratory catheter 5 (Exploratory Probe, Ice, Sao Paulo, Brazil) horizontally in the mesio-distal direction and vertically in the cervico-incisal direction of the cervical third of the selected teeth, with a light force. After stimulation, patients will be asked to point the 10-cm-long analogue visual scale (VAS) at the number that describes their perception of pain (0 = absent pain and 10 = extreme pain). After five minutes, the evaluator will apply an air stimulus: throwing a 3-second air jet of a triple syringe (Triple Syringe, Dabi Atlante, São Paulo, Brazil) with ± 40psi of pressure, directed perpendicular to the surface of the lesion and 0.5 cm apart. Protecting neighboring teeth through cotton rolls or by sealing with operator's fingers. Participants will again be asked to assign the corresponding pain score on the EVA scale

He commented that the main inclusion criterion will be the presence of two to four teeth with HD, in order to obtain groups with similar sample sizes (n) and facilitate the statistical comparison. In case the patient has more than four teeth with HD, for statistical analysis will be considered those with greater sensitivity according to EVA.

**Table 01: Selection criteria.**

| - INCLUSION CRITERIA | | ^x^ EXCLUSION CRITERIA |
| --- | --- | --- |
| - Presence of dentin exposure in anterior and / or posterior teeth - presence of two to four teeth with hypersensitive dentin, with a response ≥04 on the 10 cm long visual analogue scale (VAS). - Non-carious shallow lesion up to 2 mm deep, according to the Smith & Knight index (measured with a millimeter probe). (42) - Class I gingival recession according to Miller's classification. (43) | - Milk protein allergies; - Systemic diseases; - Presence of pulpitis; - Carious lesions; - Presence of parafunctional habits. - Presence of restorations in the cervical area, or defective in the tooth; - Presence of periodontal disease; - Presence of cracks or fractures in the enamel; - Patients in fixed orthodontic treatment; - Pregnant or lactating women; - Medication with analgesics; - Desensitizing treatment during the three months prior to the research recruitment date. | |

**6.3. Sample Calculation**

To determine the sample size of the study, data from a pilot study that followed the methodology proposed in this research project was used, with four participants, three (75% of the sample) being female and one (25% of the sample) of the sample. male, with mean age of 31 years and standard deviation of ± 1.91. In the pilot study, 16 teeth were randomly assigned to one of the four groups with the Research Randomizer Calculator (www.socialpsychology.org/randomizer.htm).

The VAS was used to measure sensitivity, considering a clinically relevant difference of three units between the initial and final VAS scores, according to a previous study (20). The G Power® program (Heinrich-Heine-Universität Düsseldorf, Germany) was used for mixed ANOVA, considering a statistical power of 80%, α error of 5% and prediction of sample loss at the end of the study of 20%. The resulting sample for this study was 80 teeth, 20 teeth per group.

[figure not shown]

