**6.5. Randomization**

The participants, with at least two teeth with HD equal or superior to four in the EVA, will be allocated through a block randomization aiming to balance the sample number in the amount of existing arms. For each block a total of four participants were defined, and after the formation of the block, a numerical draw among the participants was carried out and, subsequently, each 01 volunteer was allocated to compose one of the four groups under different arrangements (A4,1 , A3.1, A2.1 and 1) (Figure 01). The total number of blocks will be ± 10.

Allocation secrecy will be maintained throughout the sampling composition process. One of the project's collaborators will be responsible for the formation of the block, numerical draw within the block and allocation in the groups. The numerical draw will be done using numbered and coded papers, of which the participants, the principal investigator, the clinical operator and the evaluator will not be aware of the group to which the participant will be allocated.

[figure not shown]

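### The 80% power stated for 80 teeth in Protocol 6.3 is not supported for the between-arm comparison: the planning effect is a before-after change, and teeth are counted although participants are allocated.

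*Protocol*

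**What the plan says.** Section 6.3 bases the sample size on a four-participant pilot and on VAS, "considering a clinically relevant difference of three units between the initial and final VAS scores". G*Power "was used for mixed ANOVA", with 80% power, 5% alpha and 20% loss. The outcome is given in teeth: "The resulting sample for this study was 80 teeth, 20 teeth per group". The only standard deviation printed there is for age in the pilot ("with mean age of 31 years and standard deviation of ± 1.91").

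The unit of allocation varies between sections. For the pilot, 6.3 says "In the pilot study, 16 teeth were randomly assigned to one of the four groups". Section 6.4 describes the main trial as allocating teeth, with 20 per group as a floor. Section 6.5 allocates participants in blocks of four, one to each arm, and adds "The total number of blocks will be ± 10". Table 01 admits two to four hypersensitive teeth per person. The null hypothesis in section 5 is that sensitivity does not differ between the treatment groups.

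**The concern.** Two features of the calculation do not match the design.

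First, three units is the change expected in a tooth from start to finish. The hypothesis concerns the difference between arms. If the placebo arm also improves, that difference is smaller than an active arm's own change, and section 6.3 states no between-arm difference.

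Second, all study teeth of one participant receive the same treatment under 6.5. Pain scores from teeth in one mouth, reported by one person, are likely to be correlated, so 20 teeth in an arm carry less information than 20 independent observations. Section 6.3 lists its inputs and includes neither an ICC nor a number of participants.

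The risk lies in interpretation: a non-significant comparison would be read as evidence of no difference from a trial with 80% power, when the protocol does not show that it has that power.

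**Working it through.** **1. Can the stated figure be reproduced?** The loss step is consistent: 64 / 0.8 = 80 teeth, or 16 / 0.8 = 20 per arm. The 64 is inferred, and nothing leads to it, because the VAS SD, f, the correlation between repeated measurements and the tested term are all absent. Reading three units as a between-arm difference, n per arm = 2 × 7.85 × (SD/3)², where 7.85 = (1.96 + 0.84)². This gives 4, 7, 11, 16 and 22 for SD 1.5, 2, 2.5, 3 and 3.5. Only an SD near 3 yields 16, and the protocol does not state one.

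**2. How many participants?** Ten blocks × 4 = 40 participants, 10 per arm. At two teeth each that is 80 teeth, and at four each it is 160. Less 20%, 32 participants remain, 8 per arm.

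**3. Calibration.** Assume 64 independent teeth give exactly 80% power. For a one-way F test with four groups at 5%, noncentrality λ = f² × 64 on 3 and 60 df, this requires f = 0.426.

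**4. Participant-level power.** With m teeth per participant and correlation ICC, the variance of a participant's mean is σ²[1 + (m − 1)ICC]/m. Hence f_p = f × √(m / [1 + (m − 1)ICC]), and λ = 32 × f_p² on 3 and 28 df. Example for m = 2, ICC 0.3: f_p = 0.426 × √(2/1.3) = 0.529, λ = 8.95, power 64%.

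| Teeth each | ICC 0.3 | ICC 0.5 | ICC 0.7 |
|---|---|---|---|
| 2 | 64% | 57% | 52% |
| 3 | 74% | 63% | 54% |
| 4 | 79% | 66% | 56% |

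A cruder cross-check calibrates a pairwise contrast to 80% at 16 teeth per arm, then divides the number of teeth by the design effect 1 + (m − 1)ICC. With 8 participants per arm it gives 69%, 63% and 58% with two teeth each, and 82%, 71% and 61% with four.

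**5. Detectable difference.** A two-sample t test with 8 participants per arm, two-sided 5% and unadjusted, has 80% power at 1.51 participant-level SD. That is 2.3, 3.0 or 3.8 VAS units for an assumed SD of 1.5, 2.0 or 2.5.

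**6. Effect of the before-after wording.** Suppose an active arm changes by 3 units and placebo by 1.5 (an assumption). The between-arm difference is then 3 − 1.5 = 1.5. With an assumed SD of 2, pairwise power is 56% with 16 independent teeth per arm, and 41% with two teeth per participant and ICC 0.5.

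**The case against.** The strongest reply is that no printed sum is wrong and the missing inputs might be favourable. This stands in part. If the true between-arm difference were 3 units and the participant-level SD no more than about 2.0 (3 / 1.51), 8 participants per arm would give 80% power for a pairwise contrast. A reader might infer that the trial definitely lacks 80% power; with SD, f and ICC all missing, the document does not support that.

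It is also fair that the block plan may supply more than 80 teeth. With the number of participants held at 32, extra teeth raise power. At three or four teeth each and a low ICC it can exceed 80%: about 86% and 93% at ICC 0.1 by the formula in step 4.

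A reader might infer from 80 teeth at four each that recruitment could end with 20 people, five per arm. The text does not support this. Section 6.4 treats 20 teeth per group as a minimum, no section sets a stopping rule on tooth count, and 6.5 plans about ten blocks, which at two teeth each gives exactly 80.

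A reader might also infer that the pilot randomised teeth within people, so that its variance omits person-to-person differences. The pilot's allocation flowchart is not shown, and 6.4 uses similar tooth wording for a trial in which 6.5 allocates participants. Even with teeth randomised within people, a pooled within-arm SD would still contain person-to-person variance, and the protocol does not say which quantity entered G*Power. Only the unclear unit of allocation can be held against it.

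**Conclusion.** The point holds as a claim that is not supported as written. The stated effect is not the contrast in the null hypothesis, and the counted unit is not the unit allocated in 6.5. If 64 evaluable teeth was the number needed for independent teeth and each participant gives two, power is below 80% for any positive ICC; over ICC 0.3 to 0.7 the shortfall is about 16 to 28 percentage points (80 − 64 and 80 − 52). With four teeth each it is about 1 to 24 points (80 − 79 and 80 − 56).

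These sizes rest on assumed ICCs, on the inferred 64, and on a one-way F test standing in for the mixed ANOVA, whose tested term is not given. They exclude any further loss from a between-arm difference smaller than three units. That no clustering allowance was made is inferred from the inputs listed; the protocol does not say that teeth are independent.

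**What to change.** - In 6.3 and 6.5, state the sample size in participants as the ten blocks already planned: 40 randomised, 10 per arm. Keep 20 teeth per group as a minimum, not as the sample size.
- Replace the unqualified 80% power for 80 teeth with the between-arm VAS difference at one month that 8 analysable participants per arm can detect, over stated ranges of SD and ICC and for stated numbers of teeth per participant.
- Make 6.3 (including the description of the pilot), 6.4 and 6.5 agree on the unit of allocation.

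The cost is rewording three sections. It needs no participants beyond the ten blocks and no change to treatment or assessment. The downside is that the stated power will look less favourable than it does now.
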